## Abstract

**Background:**

Cardiovascular (CV) disease is the leading cause of death in women. Although 80% of CV disease events can be prevented, mortality is projected to increase, particularly in young women.

**Objectives:**

To promote CV health in women and encourage appropriate lifestyle changes by increasing awareness through vascular ultrasound imaging.

**Methods:**

WAKE UP is a prospective case-control study in a target population of 720 asymptomatic women, aged 40–70 years with ≥1 major CV risk factor (RF). Participants will attend a baseline visit and follow-up visits at 6 and 12-months. Each visit will include the assessment of traditional and non-traditional risk factors (age, blood pressure, weight, smoking, diet, physical activity, psychosocial aspects, reproductive factors, family lifestyle), CV risk scores [Fuster-BEWAT Score (FBS) and SCORE], perception of CV disease risk, blood sampling of hormones, lipids, glycemic metabolism, inflammation parameters and omics. At baseline visit, women will be randomized to undergo 2D/3D/strain vascular ultrasound (360 with imaging vs. 360 age- and RF-matched controls without imaging). Main outcomes will include changes from baseline to follow-up in overall knowledge, attitudes, and FBS.

**Conclusions:**

WAKE UP trial aims to raise awareness about womeńs CV disease and promote lifestyle changes. Imaging can play a key role by revealing the presence of atherosclerotic plaques in a directly relatable way and thus, larger effects are anticipated in women with plaques. WAKE UP can significantly impact CV prevention by involving innovative actions addressing a major public health need and by fostering complementary and synergistic actions.

## Introduction

Cardiovascular (CV) disease in women requires more attention, more research, and swifter action. It remains the leading cause of death in women, reaching 41% in Europe, 16 times higher than breast cancer (3%), corresponding to one woman deceased every minute (1, 2). The immense economic and social burden of this devastating disease is evident, including physical and psychological consequences for women and their families. Although 80% of CV events can be prevented, the trend is projected to worsen, with an alarming increase in death rate in women, especially at young age (3, 4). Nearly 50% of women aged 40–54 years have atherosclerosis, with ≥2 arterial sites affected in 26% (5). Additionally, up to 40% of index cardiac events are fatal in women (6). Thus, identifying effective preventive and diagnostic strategies is of particular importance.

CV risk in women is, however, underestimated because of the misperception that women are protected against ischemic heart disease. Lack of awareness of the importance of CV disease in women is widespread among general population and in the scientific community (7). In fact, younger women have especially low awareness rates despite high rates of CV disease burden and mortality (8). Underlying reasons for lack of awareness of women's CV risk include the following: (1) Women have been excluded from many CV clinical trials on the erroneous assumption that risk factor (RF) target values and imaging-based atherosclerosis phenotypes are similar in men and women (9); (2) Risk-stratification is especially challenging in women (8). Most women are classified at low 10-year CV risk, even in the presence of CV RF. Previous data demonstrates that all women aged 40–54 years had a low 10-year European SCORE risk (5, 10) while presenting high atherosclerosis prevalence and progression (3-year rate up to 30%) (11). Thus, although women's individual risk might be significant, they are less likely to receive guideline-indicated imaging screening or lifestyle recommendations (12); (3) Heart-disease risk in women is influenced by female-specific factors, such as age at menopause and hypertensive disorders of pregnancy, which are associated with accelerated atherosclerosis and impaired CV disease-free survival (13). However, these factors are not included in traditional risk assessments, and it is unknown if they improve risk classification independently of traditional RFs; (4) Atherosclerosis in women is under-recognized because female CV disease may have different clinical manifestations compared to men, resulting in suboptimal management. These observations highlight the need for women-specific approaches to increase awareness about CV risk and prevention.

In this article we describe the rationale and design of WAKE UP, a study aimed to improve CV disease awareness in women and healthy lifestyle promotion by using vascular ultrasound (VUS). Increasing awareness through noninvasive imaging may represent a new paradigm to bridge the gap because it reveals the presence of atherosclerotic plaques in a directly relatable way. The approach to CV disease management to date has been “inside in”, aimed at reducing RFs to minimize effects. WAKE UP is an “inside out” approach, whereby direct imaging of arterial health will be translated into specific lifestyle recommendations.

## Hypothesis and objectives

Misperception of the burden of CV disease in women is a barrier to achieving reductions in RF and atherosclerosis in women. Risk awareness will induce heart-healthy living and facilitate early recognition of symptoms. Our hypothesis is that the use of VUS will increase women's awareness, producing a greater impact on lifestyle than standard risk assessment. We predict that compliance with lifestyle recommendations would be higher among women who have undergone an imaging study because they will have seen visual evidence of their own vessel wall damage or plaque presence. This prediction is supported by the success of large evidence-based strategies that have already been conducted to promote CV health in adults and children. For example, in the TANSNIP trial, authors found that in middle-aged asymptomatic adults, a lifestyle intervention was associated with a significant improvement in CV health and behavioral metrics (14). Similarly, primordial prevention strategies in children based on school educational interventions have been shown to improve health outcomes (15). However, specific studies exploring this approach in women are lacking (16). Additionally, the identification of accurate predictors of atherosclerosis in apparently low-risk women who already have disease will help estimate individual CV risk and implement risk-reduction programs. We also aim to analyze other woman specific factors such as hormonal changes, complications during pregnancy or psychosocial factors that can influence the development of atherosclerosis. Moreover, analysis of complex data relations in a high volume of data is not an easy task, and novel data processing techniques are required.

## Methods

### Study design and population

WAKE UP is a longitudinal, prospective, case-control study that will include 720 women aged 40–70 years-old (from pre- to post-menopause) with at least one CV RF, defined as cigarette smoking, hypertension, dyslipidaemia, diabetes, obesity, poor diet, physical inactivity, family history of premature CV disease, metabolic syndrome, systemic autoimmune collagen-vascular disease, history of premature menopause, gestational diabetes or hypertensive disorders of pregnancy according to prevention guidelines for women (17). Exclusion criteria include any prior history of CV disease (myocardial infarction, angina pectoris, arrythmias, stroke, peripheral vascular disease, angioplasty, valvular heart disease, congenital heart disease or heart surgery), pregnancy and refusal to sign informed consent.

The study will include baseline, 6-month and 12-month follow-up visits (Figure 1). All visits will include traditional and non-traditional risk assessment, blood sampling and omics analysis (Table 1). Vascular imaging studies will be only performed at baseline, after randomization 1:1 for imaging risk assessment, 360 with VUS vs. 360 age- and RF-matched controls without imaging. Participants in the imaging group will be informed about their personalized CV risk based on imaging results and will be given lifestyle recommendations accordingly. Women with atherosclerotic plaque will be shown their arterial images and will be explained the meaning and CV risk associated with these findings. Those without plaques will be shown example images of atherosclerotic plaque and similar explanations will be given.

**Figure 1 F1:**
[figure not shown]
Central figure: WAKE UP study flow chart. CV, cardiovascular; US, ultrasound.

**Table 1 T1:** WAKE UP study protocol and tests included in each visit.

**Procedure**	Baseline visit	6 and 12-month follow-up visits
CV risk factors	✓	✓
CV risk scores	✓	✓
Questionnaires	✓	✓
Anthropometric measurements	✓	✓
Blood sampling	✓	✓
Omics	✓	✓
Vascular ultrasound	✓	

CV, cardiovascular.

To ensure rigorous matching in the 1:1 randomization process, participants will be stratified based on key CV risk factors prior to randomization. These factors include age, body mass index (BMI), blood pressure, lipid profile, smoking status, and family history of CV disease. Stratified randomization will be implemented to achieve balanced allocation across the imaging and non-imaging groups while accounting for these variables. Randomization will be performed using a computer-generated sequence to eliminate selection bias, with allocation concealed until the intervention assignment. By controlling for these baseline characteristics, we aim to minimize confounding and ensure comparability between groups, thereby strengthening the validity of the study's findings.

The study will be conducted in 8 Hospitals, including HM Hospitales, Hospital Universitario Fundación de Alcorcón, Hospital de Toledo, Hospital Universitario Doce de Octubre in Madrid, HM Universitario Regla in León, Hospital Universitario Marqués de Valdecilla in Santander, H. Universitario de Cabueñes in Gijón y AtriaClinic in Madrid. Core Lab for vascular imaging studies will be Atria Clinic in Madrid, and the omics analysis for Madrid will be performed in CNIC (Centro Nacional de Investigaciones Cardiovasculares Carlos III). Recruitment will be promoted at the Hospitals, Universities, Spanish Society of Cardiology and media through appropriate material distributed by different dissemination channels (informative sessions, TV, journals, etc.). We are planning to organize meetings for public and dissemination of results in means of communications to expand awareness' of CV disease in women in Society. The study protocol has been approved by the Ethics Committees of Instituto de Salud Carlos III and HM Hospitals in Madrid. Written informed consent from all participants will be obtained and archived.

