### Statistical analysis

Preliminary descriptive statistical analysis (boxplots, histograms, univariate parametric and non-parametric tests) will be used once significant amounts of data have been collected. All parameters to be collected are summarized in Table 2. We will evaluate lifestyle changes by the FBS using multivariate logistic regression. The dependent variable will be the improvement or worsening of the score between baseline and follow-up, and the analysis will be adjusted for covariates such as age to identify groups of women potentially more impacted by the imaging-based strategy. Additionally, machine learning techniques will be derived to acquire knowledge from the data. In particular, supervised and semi-supervised classifiers will be trained with 80% of the data to derive risk prediction models. Remaining 20% of the data will serve as a validation cohort. Also, clustering analysis will be performed in order to observe phenotype groups in our patients that explain the clinical variance for sample size calculation, the following formula was applied:$$n=\frac{{\left(Z_{\alpha /2}+Z_{\beta }\right)}^{2}\cdot (\;p_{1}\cdot (1-p_{1})+p_{2}\cdot (1-p_{2}))}{{\left(\;p_{1}-p_{2}\right)}^{2}}$$

**Table 2 T2:** WAKE UP study variables.

Questionnaires	
- CV risk perception	health problems, personal health conditions, CV risk and general knowledge regarding CV disease in women
- CV risk factors	smoking, hypertension, dyslipidaemia, diabetes, obesity, poor diet, physical inactivity, family history CVD, metabolic syndrome, systemic autoimmune collagen-vascular disease, preeclampsia or gestational diabetes
- Non-CV disease	Thyroid disorders, chronic renal failure, pulmonary disease, hepatic disease, cancer, autoimmune disease
- CV risk scores	FBS, SCORE, SCORE 2, ASCV, FHS 10, FHS 30
- Smoking	Age of initiation, n° of cigarettes per day, exposure to secondary smoking
- Physical activity	Hours sitting on a workday, time spent walking on a workday, practice of moderate and/or intense exercise
- Diet	Portions of carbohydrates, proteins, fruits and vegetables, dairy products, sweets, fat, water and alcohol
-Reproductive factors	Age of menarche, contraceptive use and type, complications during pregnancy, age of menopause
-Psychosocial factors	Education level, employment status, marital status, stress scale, emotional state scale

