*Z_α_*_/2_ and *Z_β_* are the critical values for the chosen significance level and power (splitting the significance level evenly between tails); *p*1 is the proportion of individuals who develop the disease without treatment, 45% according to the PESA study. *p*2 is the proportion of individuals who develop the disease with treatment, assuming 54% of our individuals will follow the provided recommendations to reduce the CVFR probability. With this setup, *n* = 481 patients will report a statistical power 1−*β* of 80% and significance level *α* of 95%, which are satisfactory in terms of clinical purposes. Given our previous experience with lifestyle intervention programs, we are well powered to detect relevant changes in the imaging group. Larger effects are anticipated in individuals with plaques, as there is more room for improvement. To account for potential variability introduced by including women across a wide age range, we will stratify participants into predefined age groups (e.g., young: 40–50 years: adult: 50–60 years, elderly: 60–70 years) during analysis. Additionally, we will apply multivariable regression models adjusted for age as a continuous variable to control for age-related confounding factors. This approach ensures that the impact of age on the progression of the atherosclerotic process is appropriately considered and mitigates the risk of contamination of information between age groups.

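### Randomisation is stratified on six factors but age is the only covariate the analysis names; an age-only model would be conservative, not biased, and the case-control label misdescribes the design

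*Protocol article*

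**What the plan says.** **Allocation.** Methods, Study design and population, places imaging "after randomization 1:1 for imaging risk assessment". The randomisation paragraph after Table 1 adds a computer-generated, concealed sequence and says: "Stratified randomization will be implemented to achieve balanced allocation across the imaging and non-imaging groups while accounting for these variables". The factors are listed as follows: "These factors include age, body mass index (BMI), blood pressure, lipid profile, smoking status, and family history of CV disease".

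**Outcome.** Clinical data collection and risk scores defines the FBS from blood pressure, exercise, weight, diet and tobacco, each graded 0 to 3. Follow-up and end-points makes change in FBS from baseline the primary endpoint.

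**Analysis.** Statistical analysis plans a logistic regression of FBS improvement or worsening, in which "the analysis will be adjusted for covariates such as age". Later in the same section, on the wide age range: "we will apply multivariable regression models adjusted for age as a continuous variable". No other stratification factor is named as a covariate.

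**Label.** The same section that randomises the women opens with "WAKE UP is a longitudinal, prospective, case-control study that will include 720 women" and describes the arms as "360 with VUS vs. 360 age- and RF-matched controls without imaging". The Abstract uses the same terms.

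**The concern.** Stratified randomisation makes the arms more alike on the stratification factors than chance would. If those factors predict the outcome, the treatment estimate varies less from trial to trial. A model that leaves them out does not credit that balance, so its standard error is too large and some power is lost.

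There is reason to expect that some of the factors are prognostic. A woman already graded 3 on a component cannot improve on it, so baseline blood pressure, weight and smoking partly set her room to improve. The article reasons in the same way about women with plaques.

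The label is a separate matter. Nobody is selected by outcome and no pairs are formed. Calling a concealed 1:1 randomised comparison a case-control study with matched controls contradicts the described allocation and undersells the evidence.

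**Working it through.** **1. The plan's own figure.** The only computed figure is the sample size. It is reproduced here because it supplies the effect size used below. Inputs from Statistical analysis: p1 = 0.45, p2 = 0.54, power 80%, two-sided significance level read as 0.05.

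n = (1.960 + 0.842)² × (0.45×0.55 + 0.54×0.46) / 0.09² = 7.849 × 0.4959 / 0.0081 = 480.5, rounded up to 481.

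The printed formula gives a number per arm. With 360 per arm, power on these inputs is about 68% before any dropout. The sample size is a different point, but it shows that there is little power to spare. The corresponding odds ratio is (0.54/0.46)/(0.45/0.55) = 1.43.

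**2. Overlap of design, outcome and model.**

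| Stratification factor | FBS component | Named as covariate |
|---|---|---|
| Age | no | yes |
| BMI | yes (weight) | no |
| Blood pressure | yes | no |
| Lipid profile | no | no |
| Smoking status | yes (tobacco) | no |
| Family history | no | no |

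**3. What an age-only model would cost.** The simulation has 720 women and 2,500 runs per setting. The article gives no cut points, block size or prognostic strength, so these are assumptions: six two-level factors (2⁶ = 64 strata, 720/64 = 11.25 women each), permuted blocks of 4 within strata, control probability centred at 0.45, and the same conditional log-odds ratio for every factor.

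| Log-odds ratio per factor | 0 | 0.3 | 0.6 | 0.9 |
|---|---|---|---|---|
| Mean SE / true SD, age only (no effect) | 0.1501/0.1465 = 1.02 | 0.1505/0.1477 = 1.02 | 0.1514/0.1421 = 1.07 | 0.1525/0.1397 = 1.09 |
| Type I error, age only | 4.5% | 4.2% | 3.8% | 3.4% |
| Type I error, all six | 4.6% | 4.4% | 4.6% | 4.8% |
| Power at OR 1.43, age only | 66.4% | 65.4% | 57.0% | 50.3% |
| Power at OR 1.43, all six | 67.1% | 67.0% | 60.5% | 58.6% |
| Power difference (points) | 0.7 | 1.6 | 3.6 | 8.3 |

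Simulation error is about 0.015 on the SE ratio and √(0.05×0.95/2500) = 0.4 points on type I error. The first column is therefore compatible with no effect at all, and the second nearly so. The shortfall is clear only at 0.6 and 0.9. Power should be compared within a column: it falls from left to right in both models because 1.43 is held fixed as a conditional odds ratio, which means a smaller difference in proportions when the factors are strong.

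**4. Baseline FBS.** This step uses a linear approximation with equal variances at baseline and follow-up and correlation r (assumed). The variance of a change score is proportional to 2(1−r), and that of a baseline-adjusted comparison to 1−r². The reduction is 1 − (1−r²)/[2(1−r)] = (1−r)/2, which is 25% at r = 0.5 and 15% at r = 0.7. This is indicative only, because the stated model is logistic.

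**The case against.** The strongest reply is that the article never fixes an age-only model. Its covariate wording is illustrative, the sentence on continuous age serves the separate purpose of handling a wide age range, and a full covariate list normally belongs in an analysis plan that is not shown. This stands. The most that can be said is that the text names no stratification factor except age.

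A reader might go further in four ways that the document does not support:

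- *The error bars are wrong because the study is called case-control.* No matched-pair, conditional or case-control analysis is described, so the label alters no standard error.
- *The results would be biased or produce false positives.* Omitting balanced factors errs in the conservative direction, and no bias between arms follows.
- *The intervals would be 5 to 20% too wide.* The linear formula 1/√(1−R²) gives 1.054 at R² = 0.10 and 1.195 at R² = 0.30. It treats all six factors as omitted although age is adjusted for, assumes complete balance, and does not apply to the planned logistic model. A baseline-adjustment gain of 25 to 49% (r² at r = 0.5 to 0.7) likewise compares with an unadjusted follow-up analysis, which is not planned.
- *Leaving out the eight hospitals breaks the design.* Hospital is not among the stated stratification factors.

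It is also fair to say that the article gives no strength of association between these factors and change in FBS. The room-to-improve argument makes one plausible but does not measure it.

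**Conclusion.** The point holds as a moderate one about precision and description, not about validity. Three facts rest on the text alone: six stratification factors, three of them overlapping the primary outcome; age as the only named covariate; and a design label that contradicts the stated randomisation.

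The size is conditional on age being the only covariate used. In that case, over assumed log-odds ratios of 0 to 0.9 per factor, the standard error is overstated by about 0 to 9%, type I error is about 4.5 to 3.4% against a nominal 5%, and power is lower by 0.7 to 8.3 points (1 to 9 if the rounded percentages are subtracted). If the factors do not predict FBS improvement, nothing is lost. These figures also rest on the assumed two-level factors and blocks of 4.

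**What to change.** 1. In Statistical analysis, state that the primary FBS model compares the arms as randomised and includes all six stratification factors (continuous where they are measured so) and baseline FBS. If the model stays logistic, state that the odds ratio is conditional on these covariates.
2. In the Abstract and in Study design and population, replace case-control and matched controls with stratified randomised parallel-group trial, and describe the randomisation step as stratification, not matching.
3. Adding hospital as a covariate is optional.

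The cost is wording only. The article already collects all six factors and the FBS at the baseline visit, so no new data, visits or participants are needed.

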### Clinical data collection and risk scores

Each woman will undergo assessment of blood pressure, weight and body composition as well as a 1-h interview including all study questionnaires. A standardized 38-item questionnaire with a mix of Likert scale, open-end, and recognition questions will be used to assess CV risk perception. Similar to the American Heart Association National Survey (18), questions will be divided into 4 sections: general awareness of women's health issues; communications and behaviours related to CV disease prevention; specific understanding of CV disease and behaviours associated with prevention; and demographic characteristics. Smoking will be assessed by adults' tobacco use questionnaire from the National Health Interview Survey (NHIS) (19).

Diet will be assessed by a 14-item MEDAS (Mediterranean Diet Adherence Screener) questionnaire, used in the PREDIMED study that analyzes the consumption of the main components of the Mediterranean diet and their recommended amounts (20). Physical activity will be assessed by International Physical Activity Questionnaires (IPAQ) short version that assesses the types of intensity of physical activity and sitting time (21). Psychosocial and sleep aspects will be collected by the CES-D (Center for Epidemiological Studies-Depression), a 20-item questionnaire aimed at identifying individuals at risk for clinical depression with good accuracy across wide age ranges (22) and by a 12-item questionnaire that includes sleep habits, quality of sleep, and sleepiness (23). Women will be also asked about reproductive factors (age of menarche and menopause, contraceptive use, pregnancy, preeclampsia, gestational diabetes, preterm birth), family lifestyle (educational background, perception of family member medical conditions) and non-CV disease.

Several scores will be calculated to assess CV risk: Fuster BEWAT score (FBS) (24) compiles 5 variables (blood pressure, exercise, weight, alimentation, and tobacco) into a 15-point ordinal scale. For each variable, a numeric grading system (0, 1, 2, or 3) has been adopted in relation to international guidelines, being 3 the optimal value. Systemic Coronary Risk Estimation (SCORE) algorithm will be used to estimate risk of fatal CV disease by gender, age, systolic blood pressure, total cholesterol and smoking status (25). SCORE2 is an update of the original SCORE algorithm derived, calibrated, and validated to predict 10-year risk of first-onset CV disease by enhancing the identification of individuals at higher risk of developing CV disease across Europe (26). Atherosclerotic CV disease (ASCVD), based on age- and sex-specific pooled cohort equations estimates 10-year risk of nonfatal myocardial infarction, coronary heart disease death, or stroke for asymptomatic adults 40–75 years of age (27). Ten- and 30-year Framingham Risk Scores (28, 29) predict risk of hard coronary heart disease (coronary death, myocardial infarction, stroke).

